## Abstract

**Background:**

Ileostomy closure is associated with a high rate of postoperative morbidity, and adynamic ileus is the most common complication, with an incidence of up to 32%. This complication is associated with delayed initiation of oral diet intake, abdominal distention, prolonged hospital stay, and more significant patient discomfort. The present study aims to evaluate the rectal stimulus with prebiotics and probiotics before ileostomy reversal.

**Methods:**

This is a protocol study for an open-label randomized controlled clinical trial. Ethical approval was received (CAAE: 56551722.6.0000.0071). The following criteria will be used for inclusion: adult patients with rectal cancer stages cT3/4Nx or cTxN+ that underwent loop protection ileostomy, patients treated with neoadjuvant chemoradiotherapy, and patients who underwent laparoscopic or robotic total mesorectal excision. Patients will be randomized to one of two groups. The intervention group (with rectal stimulus): the patients will apply 500 ml of saline solution with 6 g of Simbioflora® rectally, once a day, for 15 days before ileostomy closure. The control group (without rectal stimulation): the patients will close the ileostomy with no previous rectal stimulus. The primary outcomes will be the adynamic ileus (need for postoperative nasogastric tube insertion; nausea/vomiting; or intolerance to oral feedings within the first 72 h) and intestinal transit (time to first evacuation/flatus).

**Results:**

The patient’s enrollment starts in January 2023. We expect to finish in July 2025.

**Discussion:**

The findings of this randomized clinical study may have important implications for managing patients undergoing ileostomy reversal.

**Trial registration:**

This study is registered in the Brazilian Trial Registry (ReBEC) under RBR-366n64w. Registration date: 19/07/2022

## Background

A protective ileostomy is a temporary measure usually applied to reduce the severity of complications related to colorectal anastomosis in patients with rectal cancer undergoing neoadjuvant chemoradiotherapy [1]. However, ileostomy closure is associated with a high morbidity rate, and adynamic ileus is the most common complication, with an incidence of up to 32% [2–12]. This complication is associated with delayed initiation of oral diet intake, abdominal distention, more significant patient discomfort, and prolonged hospital stay [13]. The probable cause is colonic dysfunction, leading to mucosal atrophy, with the consequent loss of intestinal absorptive capacity and atrophy of intestinal muscles, inducing changes in intestinal peristalsis [14].

Abrisqueta et al. [12], in a clinical trial of 70 patients, showed that patients that stimulated the efferent ileostomy loop with 500 ml of saline plus a thicker agent (Nestlé Resource, Vevey, Switzerland) 2 weeks before ileostomy closure had a shorter time for diet acceptance (1.06 *vs.* 2.57 days), shorter mean time to defecation (1.14 *vs.* 2.85 days), lower rate of adynamic ileus (3% *vs.* 20%), and shorter hospital stay (2.5 *vs.* 4.6 days). However, the study encompassed a limited sample size, including both primary open and laparoscopic surgery. Open primary surgery can falsify the diagnosis of adynamic ileus since intestinal adhesions can contribute to postoperative food intolerance [15].

Rodríguez-Padilla et al. [16], in a recently published randomized clinical trial, evaluated 69 patients. The intervention group had the efferent ileostomy loop stimulated with probiotics (Vivomixx®). The study demonstrated a decrease in the severity of colitis. However, there was no clinical implication for this finding (the groups showed similarities in the length of hospital stay, adynamic ileus, and time to the first defecation). It is noteworthy that Rodríguez-Padilla et al. [16] performed a per-protocol (not intention-to-treat) analysis, and the primary outcome was colitis rate. The sample size was estimated based on the presumed difference in colitis rates between the groups, which does not necessarily imply clinical repercussions. Thus, the differences between the groups for the length of stay and time for diet acceptance probably did not present enough power (1-beta) to conclude a non-significant clinical relevance for intestinal stimulation. Per-protocol analyzes are weak for clinical practice inferences, especially in a study protocol in which the intervention depends on the patient's active participation (which can be erroneous) to infuse the substances that will stimulate the efferent loop.

In an observational study, Liu et al. [17] evaluated outpatients that self-administered reinfusion with *succus entericus* prior to ileostomy closure. The group that received *succus entericus* showed a significantly shorter time to first flatus or stool (27.9 *vs.* 32.3 h), shorter length of hospital stay (4.9 *vs.* 5.52), and better low anterior resection scores (LARS).

These previous studies evaluated the excluded intestinal stimulus via the efferent ileostomy loop. However, self-delivering substances through ileostomy are not usual for outpatients, who may fail to stimulate excluded intestinal loop appropriately, creating complexity in interpreting the results. The stimulation of the rectum was not evaluated in these previous trials. Rectal enemas are often used and tolerated as routine treatment for several conditions, such as inflammatory bowel disease and chronic constipation [18–21]. Consequently, theoretically, enemas could be easier for patients to adhere to an excluded intestinal stimulus protocol.

We hypothesized that a rectal administration of prebiotics and probiotics may significantly impact colitis amelioration and could be well tolerated. Besides, since the rectum and colon work as a reservoir [22], their direct stimulus to the mucosal could theoretically improve clinical outcomes.

Considering the heterogenic findings among previously published trials regarding the value of intestinal stimulus with prebiotics and probiotics and the lack of a clinical study evaluating direct stimulation by the rectum, a high-quality randomized trial is needed.

### Objectives

The present study is a protocol for a 1:1 parallel-randomized superiority clinical trial that aims to evaluate, with an intention-to-treat analysis, the value of rectal stimulation with prebiotics and probiotics before ileostomy closure. We hypothesized that rectal stimulation with prebiotics and probiotics before ileostomy closure could reduce the incidence of adynamic ileus and improve patients’ postoperative clinical and functional outcomes. The findings of this study may have important implications for the future management of patients undergoing ileostomy reversal.

## Methods

The SPIRIT 2013 [23] guidelines were followed for the construction of this report (Fig. 1).

**Fig. 1 Fig1:**
[figure not shown]
SPIRIT. Schedule of enrolment, interventions, and assessments

### Study design

This study will be an open-label parallel-randomized superiority controlled clinical trial.

### Study settings

Patients will be recruited from a public oncological surgery teaching hospital, and all procedures will be performed in this same hospital (Hospital Municipal Vila Santa Catarina, São Paulo, Brazil).

### Ethics and registration

The study’s protocol followed the Helsinki statements and was approved by the local ethics committees (Hospital Israelita Albert Einstein; CAAE: 56551722.6.0000.0071; CEP 5.475.035). The protocol was registered in the Brazilian Registry of Clinical Trials (ReBEC) under the identifier RBR-366n64w. All participants will sign the Free and Informed Consent Form.

### Eligibility

The inclusion criteria are patients that (1) are adults (> 18 years), (2) with rectal cancer in clinical stages cT3/4Nx or cTxN+, (3) treated with neoadjuvant chemoradiotherapy, (4) submitted to laparoscopic or robotic total mesorectal excision and submitted to loop protection ileostomy, and (5) who are not undergoing systemic chemotherapy.

The exclusion criteria are patients that (1) refuse to participate in the study; (2) with a history or suspicion of inflammatory bowel disease (typical endoscopic findings at diagnosis, including marked erythema, loss of vascular marking, erosions, ulcers, and spontaneous bleeding); (3) pregnant; or (4) who have any contraindication for general anesthesia or surgical intervention.

All patients from our institution will be evaluated consecutively, and the ones that fit the eligibility criteria will be invited to participate in the study. To be transparent during the selection process, we will document every patient that does not accept to participate.

### Sample size

Assuming that the intervention will reduce the adynamic ileus incidence after ileostomy reversal from 20 to 2.8% [12], the estimated sample is 52 patients in each study arm, considering alpha (two-sided) 0.05 and beta 0.2 [24]. Considering that our primary outcome will be a short-term endpoint, evaluated during hospitalization after surgery, we do not expect a significant loss of follow-up for the primary outcome.

### Randomization

Patients will be consecutively evaluated, and the eligible patients will be invited to participate in the research project. If the patient agrees to participate in the project, the researchers will instruct about the risks and benefits of the study and will be given the printed Free and Informed Consent Term for signature. The patients will be advised that they may interrupt their participation in the research at any time. One copy will remain with the patient and the other with the research team.

The researchers will use Microsoft Excel’s random number generation function to perform a 1:1 block randomization. Blocking will ensure a close balance of the numbers in each group at any time during the trial. Knowing that investigators could deduce some of the subsequent treatment allocations if he or she knows the block size, we will use large block sizes (8–12) and randomly vary the block size to ameliorate this issue. The randomization sequence was not concealed. There is no plan for interim analysis.

Patients will be randomly assigned to the intervention group (with rectal stimulus) or the control group (without rectal stimulus). See Fig. 2.

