### Statistical analysis

An independent author not involved in the recruitment or data collection will perform an intention-to-treat analysis in this superiority controlled trial. Improper application of the rectal tubes will not be excluded from the analysis. The patients will be analyzed according to the group assigned in randomization, even if they drop the intervention or apply only partially (or incorrectly) the rectal stimulation solution. Qualitative variables will be described as absolute counts and percentages. Continuous variables will be described as median and interquartile range. Scores outcomes generated from questionnaires will be evaluated as discrete variables. Differences between groups will be evaluated by the Mann-Whitney test for continuous and discrete variables and Fisher’s exact test or chi-square test for categorical variables. No adjustments per baseline characteristics of the patients are intended.

The investigators will check monthly to ensure the integrity of the data quality, assessing for missing data and invalid field entries. The mean of each variable will be used to replace missing data. The Kolmogorov-Smirnov test will be used to investigate the normality distribution of the variables. For non-normal distribution, a logarithmic transformation will be performed. For sensitivity analysis, the best-worst-case scenario dataset will be generated, assuming all participants lost to follow-up in the intervention group have had a beneficial outcome and all those with missing outcomes in the control group have had a harmful outcome. Then a worst-best-case scenario dataset will be generated assuming all participants lost to follow-up in the intervention group have had a harmful outcome, and all those lost to follow-up in control have had a beneficial outcome. For continuous outcomes, a “beneficial outcome” will be the group mean plus 2 standard deviations of the group mean, and a “harmful outcome” will be the group mean minus 2.

A per-protocol analysis, in which participants who violate the protocol are excluded from the analysis, will be performed as sensitivity analysis to investigate the robustness of the results to protocol deviations.

Statistical analyzes will be performed using the Statistical Package for the Social Sciences, version 18.0 for Windows (SPSS Inc., Chicago, IL, USA).

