### Data monitoring and management

The researchers will perform data collection. The data will be stored in a secured database using protected pathways. All data is anonymous. Only the research team will have access to the data set.

Independently on the findings of the present study, we intend to publish it in a peer-review journal. The local ethics committee does not require a data monitoring committee since only low-risk interventions will be performed. However, an audition may be performed at the discretion. No interim analyses are planned. The only stopping guideline is when the planned sample size is reached.

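### The protocol states that the randomization sequence was not concealed, which cancels its own block-size precaution and leaves enrolment unprotected against selection bias

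*Protocol article*

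**What the plan says.** The Randomization section of the protocol article assigns the list to the research team: "The researchers will use Microsoft Excel’s random number generation function to perform a 1:1 block randomization". It recognises that blocks can be predicted ("Knowing that investigators could deduce some of the subsequent treatment allocations if he or she knows the block size") and gives its answer: "we will use large block sizes (8–12) and randomly vary the block size to ameliorate this issue". The next sentence reads: "The randomization sequence was not concealed". The article describes no envelopes, central service or third party that would release allocations.

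The same section says of the consent discussion that "the researchers will instruct about the risks and benefits of the study", and Data monitoring and management says "The researchers will perform data collection". The only stated independence is at the analysis stage: "An independent author not involved in the recruitment or data collection will perform an intention-to-treat analysis".

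Four other statements bear on the point:
- Study design: "This study will be an open-label parallel-randomized superiority controlled clinical trial".
- Eligibility: the institution's patients are assessed consecutively, and those who decline are recorded.
- Statistical analysis: no adjustment for baseline characteristics is intended.
- Discussion: the limitations listed are the fixed 15-day stimulation period, the single centre and the absence of blinding. Lack of concealment is not among them.

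**The concern.** Concealment keeps the person who decides whether and when to enrol a patient from knowing which arm comes next. Without it, a randomly generated list can still produce groups that differ systematically, because the choice of patient for each slot is no longer independent of the slot.

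This trial leaves room for that. Two exclusions call for judgement: suspected inflammatory bowel disease, and any contraindication to anaesthesia or surgery. The reversal date has a minimum interval after the first operation but no fixed day, so the time of approach can move. The intervention asks patients to give themselves an enema daily for 15 days, and the Discussion says that such co-operation is often hard to obtain. A recruiter who knew the next arm could, without any bad intent, favour a co-operative patient for an intervention slot.

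Intention-to-treat analysis keeps patients in the arm to which they were assigned. It cannot correct an assignment that was selective from the start, and the unadjusted primary comparison would carry any imbalance straight into the result.

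**Working it through.** **1. The plan's own figure.** Sample size gives 52 per arm for 20% against 2.8%, two-sided alpha 0.05, power 80%. With pooled variance under the null and no continuity correction, and mean proportion (0.20 + 0.028)/2 = 0.114:

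n = [1.960 × √(2 × 0.114 × 0.886) + 0.842 × √(0.20 × 0.80 + 0.028 × 0.972)]² / 0.172² = 52.4, or 53 when rounded up.

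Power at 52 per arm is 79.7%. The figure reproduces to within one patient. It does not depend on concealment: the issue is bias, not size.

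**2. The two adjacent statements.** The stated purpose of varying the blocks is to stop investigators deducing the next arm. Deduction matters only to someone who cannot read the list. How predictable is the next arm in each case?
- List readable: the next arm is known every time, whatever the block sizes.
- List concealed, past allocations known: I simulated 10,000 sequences of 104 patients, assuming block sizes 8, 10 and 12 equally likely and no strata. Guessing the arm that is behind in the running count, and tossing a coin at ties, is right about 65% of the time.
- Pure chance: 50%.

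The block precaution therefore has value only if the list is concealed, which the following sentence denies.

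**3. What the existing safeguards reach.** Consecutive evaluation and the record of refusals are set against the routes by which foreknowledge could act:
- Patient invited and declines: recorded.
- Patient judged ineligible on a discretionary criterion: no record described.
- Patient approached earlier or later: no record described.

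**4. Hypothetical size.** Assume two types of patient with ileus risks of 32% and 8%, in equal numbers overall (average 20%, the planned control rate), and no treatment effect. The 32% equals the upper end of the incidence range quoted in the Background, used here only as a convenient high value. The 8% is chosen so that the average is 20%. Neither is a documented subgroup rate.

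- Control arm 60% high-risk, intervention arm 40%: 0.6 × 0.32 + 0.4 × 0.08 = 0.224, and 0.4 × 0.32 + 0.6 × 0.08 = 0.176. Difference 4.8 points, or 4.8/17.2 = 28% of the planned effect (20 − 2.8 = 17.2 points).
- Control arm 70%, intervention arm 30%: 0.248 and 0.152. Difference 9.6 points, or 56% of the planned effect.

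Treating each arm as binomial with 52 patients, the chance of p ≤ 0.05 with no treatment effect is:

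| High-risk share, control / intervention | Fisher's exact | Chi-square, uncorrected |
|---|---|---|
| 50 / 50 | 2.9% | 5.0% |
| 60 / 40 | 6.0% | 9.4% |
| 70 / 30 | 16.8% | 23.2% |

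Statistical analysis allows either test.

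**The case against.** The strongest reply is that the sentence may not mean what it says. A team that varies its block sizes to defeat prediction is unlikely to leave the list open, and in an open-label trial the authors may have used *not concealed* loosely for *not blinded*. That is plausible, but it does not remove the point. Blinding and concealment are separate, an open-label trial can be fully concealed, and no method of concealment is described. The sentence needs correcting on either reading.

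A second reply is that consecutive evaluation and the record of refusals already restrain selective enrolment. They do, and they deserve credit. They do not reach eligibility decisions or timing.

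Several stronger inferences are tempting, and the document does not support them:
- That recruiters do consult the list, or that bias has occurred. Nothing says who holds the list.
- That the same individuals generate the list, recruit and collect data. The article uses one collective term for all three. It is fair to say only that no separation is described.
- That baseline adjustment is forbidden. It is only not intended.
- That the spreadsheet may recalculate and change the list. Whether the values are frozen is an operational detail that an article would omit.
- That the symptom-based primary outcome makes this worse. That concerns unblinded assessment, which concealment would not change.

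The numerical illustration is also open to challenge. The document names no prognostic marker that would let recruiters sort patients sharply, and a 70/30 split would be extreme under consecutive invitation. At 60/40 with Fisher's exact test, the error rate of 6.0% is only slightly above nominal.

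**Conclusion.** The point stands in conditional form. The protocol affirmatively says that the sequence was not concealed, and nothing elsewhere in the article withdraws or qualifies it. Taken literally, this makes the varied blocks pointless and leaves the trial without protection against selection bias at enrolment. Because it is a positive statement, it cannot be treated as a detail left to a fuller document.

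No size of bias can be derived from the protocol. The 4.8-point difference rests entirely on the assumed 32% and 8% risks and the assumed 60/40 imbalance. It shows what moderate steering could do and is not a forecast. The conclusion does not depend on it. The sentence must be changed because selective assignment cannot be reliably undone at analysis and the preventive step is cheap.

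**What to change.** Replace the sentence with a rule along these lines: *The sequence is generated once and held by a person not involved in recruitment or outcome collection and, preferably, not in the analysis. Each allocation is released only after the patient has consented and has been irreversibly logged as enrolled, for example by opening the next sequentially numbered, opaque, sealed envelope.* The independent analyst already named could hold the list, but that would draw the analyst into trial conduct, so another holder is better.

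If the authors meant that the trial is not blinded, the sentence should say that and then state how allocation is concealed.

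Enrolment was planned from January 2023 into 2025, so some or all patients may already have been allocated; the article cannot show this. For any allocated without concealment:
- report how many there were;
- compare baseline characteristics by arm;
- add a baseline-adjusted sensitivity analysis;
- add the lack of concealment to the limitations in the Discussion.

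The cost is an amendment to the protocol and registry entry, a set of envelopes or an equivalent release step for each patient, and one secondary analysis. The sample size and the primary analysis do not change.

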**Fig. 2 Fig2:**
[figure not shown]
Allocation flow diagram

### Study groups

Intervention group (with rectal stimulation): The patient will receive guided instruction in an outpatient setting. The patient will receive the necessary materials, which include 14-French rectal tubes, saline, and a source of soluble prebiotic fibers (fructooligosaccharide) with probiotics (*Lactobacillus acidophilus*, *Lactobacillus rhamnosus*, *Lactobacillus para casei*, *Bifidobacterium lactis*) (Simbioflora®; Brand: Invictus; Manufacturer: Farmoquimica; MS1666370001001 Registry). The patient will apply 500 ml of saline solution with 6 g of Simbioflora® rectally, once daily, for 15 days before the ileostomy reversal surgery. The saline solution vials will have a predetermined volume (500 ml) to guarantee that the patients use the correct volume. The patient will have weekly visits, and the researchers will provide a contact for service at any time to optimize patients’ adherence.

Control group (without rectal stimulus): The patient will be submitted to the ileostomy reversal with no previous rectal stimulus. No placebo will be applied.

In both groups, patients will be instructed to record colic/abdominal pain symptoms, nausea/vomiting, diarrhea, and gas during the 15 days prior to ileostomy closure.

